#### Cluster Randomized Trial

The baseline assessment was conducted following enrollment into the cash transfer program in a confidential environment in preidentified venues in the respective villages. Following the informed consent procedures and eligibility assessment, a structured self-administered questionnaire was administered to trial participants using ACASI. Data were collected on demographics, factors related to HIV vulnerabilities, family planning, sexual risk behavior, and GBV. All trial participants were asked to give a blood specimen for HIV and HSV-2 infection determination. Participants underwent pretest counseling, HIV test, and receive HIV test results on the same day after posttest counseling according to national HIV testing algorithms. HSV-2 infection determination was conducted at the National Institute for Medical Research (NIMR) Mwanza laboratory using the enzyme-linked immunosorbent assay technique, and the results were communicated to the participants within 2 weeks. HSV-2 test results include posttest counseling and referral for treatment of HSV-2, where needed.

Following the delivery of the intervention in the intervention clusters, the first follow-up survey (6 months after the baseline), second follow-up (12 months after the baseline), and third follow-up (18 months after the baseline) are undertaken in both clusters over 1 month. Follow-up surveys are performed in a preidentified venue used during the baseline assessment. Participants’ data and blood specimen are collected at follow-up visits (6, 12, and 18 months) as well. Data and blood specimens collected are linked to the AGYW by a unique participant identification number. The interview is conducted in a private area to ensure confidentiality and anonymity of the information collected.

#### Qualitative Components

PGDs and case studies are used to collect qualitative data. PGDs describe perceptions and preferences of different intervention packages, whereas case studies are used to track in detail a small cohort of 20 AGYW purposely selected to monitor and unearth the dynamics involved in delivery and uptake of cash transfer. PGDs are used to collect data during the baseline survey, whereas case studies follow-ups selected participants in the intervention arm only at more regular intervals (every 6 months).

A total of 6 PGDs (3 intervention and 3 control PGDs) are conducted at baseline. Each PGD comprises 8 to 10 AGYW. Participants for the PGDs are randomly selected and approached to participate. Inclusion criteria for the PGDs include willingness to participate in a PGD; consent from the participant and parent or guardian, if applicable, as documented by written informed consent; and enrollment in the trial with complete baseline ACASI questionnaire.

Qualitative data gathering and analysis are performed as a continuous, flexible, and iterative process. Preliminary data collected through case studies are analyzed in the field (sequential analysis), after which further analysis of texts is performed to confirm or refute interim results through constant validity checks until saturation is reached.

### Outcomes

End points are assessed at baseline and after every 6 months over the next 18 months. The primary outcome measure is the incident HSV-2 infection. Secondary outcome measures include HIV prevalence, reporting of intergenerational sex (sexual partnership between AGYW and a man 10 or more years older), and reporting of compensated sex (AGYW are asked to report whether they have received money or gifts in exchange for sex) in the last 6 months. Compensated sex is assessed by self-report of whether AGYW has had sex with anyone because they received money or gifts or because they expected to receive money or gifts. The primary exposure is cash transfer received. Table 3 presents the outcomes, indicators of change of outcomes, and uptake of interventions.

**Table 3 table3:** Outcomes, indicators of change of outcomes, and uptake of interventions.

Factor	Variables
Primary and secondary outcomes	Herpes simplex virus type 2 incidence, HIV prevalence, reporting of intergenerational sex, Compensated sex
Indicators for change	Increased comprehensive HIV prevention knowledge, increased income and savings, increased confidence to accept an HIV test, increased confidence to negotiate condoms with nonmarital partners, and increased access to biomedical interventions (community-based HIV testing and counseling services plus, sexually transmitted infection, gender-based violence, and substance and alcohol screening and family planning)
Uptake of Sauti interventions	Individuals who received interventions or control packages; within the intervention sites, individuals who received (1) SBCC^a^, cash transfer, WORTH+^b^ and (2) cash transfer and combination prevention interventions; and within the control sites, individuals who received (1) SBCC and WORTH+ and (2) combination prevention interventions

^a^SBCC: social and behavior change communication.

^b^WORTH+: Women Organizing Resources Together Plus.

### Data Management

The data from ACASI and qualitative interviews are collected using tablets and digital audio recorders, respectively. Data are directly transferred to the NIMR cloud storage at the end of each working day. The site supervisor synchronizes the data to the cloud. A specialized data person with permission to access data in the cloud extracts all study data and uploads them to NIMR data management system for further data cleaning and production of analytical datasets. All sound files are deidentified, transcribed, and translated before analysis.

All quantitative data are managed and cleaned in Stata (StataCorp, College Station, Texas) version 13 [32], whereas qualitative data analyses are cojointly performed by coinvestigators using NVivo software (QSR International, Melbourne, Australia) [33]. Data validation checks to identify errors and inconsistencies are programmed and run in Stata. Data queries are raised on data clarification forms and sent to the field to the appropriate member of the study team to be resolved; when a query is resolved, the database is updated accordingly. After data are clean, ACASI and laboratory data are merged using the unique study number. All electronic data are stored in password-protected database systems. There is also hardware password protection on computers, servers, and networks. All printed transcripts and paper-based forms are securely locked up in the filing cabinet with limited access.

### Statistical Analysis

#### Sample Size

CRT is powered to detect intervention impact on the reduction of new HSV-2 infections. HSV-2 incidence was chosen as a proxy measure for HIV incidence, as the study would not be powered to detect a difference in HIV incidence in a relatively low-incidence setting such as Tanzania. A study conducted among women working in the food and recreational facilities, in a setting similar to one in this study, found an HSV-2 incidence of 35.2 per 100 person-years and 24.2 per 100 person-years among women aged 18-19 years and 20-24 years, respectively [34].

All sample size calculations were performed using methods for matched cluster randomized trials. A sample of 15 paired clusters (30 clusters) with 70 AGYW per cluster achieves >80% power to detect a difference of –0.07 between the intervention HSV-2 incidence of 13% and the control HSV-2 incidence of 20% in an 18-month period. The between-community coefficient of variation in HSV-2 incidence was assumed to be 0.25 [35], and the significance level of the test is 0.050. The sample size (70 AGYW per cluster) has been increased by 48% to 104 AGYW per cluster (1560 per arm) to account for attrition rate and background HSV-2 prevalence. It is estimated that, at baseline, HSV-2 prevalence will be 20% among AGYW aged 15-23 years [34]; the attrition rate is 10% and the nonresponse rate is 18% over 18 months.

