### Eligibility Criteria for Clusters

Clusters in the selected councils were eligible for the trial if they were receiving Sauti interventions other than cash transfer and had at least 110 AGYW aged 15-23 years who were out of school according to the household survey conducted in all villages/*mitaa*, which were identified as potential villages to receive the CTP. Eligible clusters were randomized before implementation of the CTP.

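### The inflation from 70 to 104 per cluster adds up loss rates instead of dividing by the retained fraction; at the plan's own rates 104 enrolled gives about 61 analysable per cluster, and power of about 80% instead of 83%

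*Protocol article*

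**What the plan says.** All of the design figures are in the Sample Size section of the protocol article.

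- **Method:** "All sample size calculations were performed using methods for matched cluster randomized trials".
- **Power claim:** "A sample of 15 paired clusters (30 clusters) with 70 AGYW per cluster achieves >80% power", for "a difference of –0.07 between the intervention HSV-2 incidence of 13% and the control HSV-2 incidence of 20% in an 18-month period".
- **Other inputs:** "The between-community coefficient of variation in HSV-2 incidence was assumed to be 0.25", and "the significance level of the test is 0.050". Whether the test is one- or two-sided is not stated.
- **Inflation:** "The sample size (70 AGYW per cluster) has been increased by 48% to 104 AGYW per cluster (1560 per arm"). The stated purpose is to allow for attrition and background HSV-2 prevalence.
- **Rates:** baseline HSV-2 prevalence is put at 20%, and "the attrition rate is 10% and the nonresponse rate is 18% over 18 months".

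Three other places fix what the 104 has to cover. Participant Recruitment keeps women who test HSV-2 positive at baseline in the study, so they take up enrolled places. Statistical Methods defines the primary analysis on women who were HSV-2 negative at baseline, by their status at 18 months. Study Strengths and Limitations gives the total as 3120, which is 30 x 104.

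**The concern.** The three rates add to exactly 48%, and 70 x 1.48 rounds up to 104. That treats each loss as a percentage of the 70 women needed at the end. In fact each is a percentage of the women who enter, or of those still present at that stage. Adding loss percentages to the target always under-recruits, and the gap widens as the losses grow. With losses of this size it is no longer trivial.

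A woman counts in the primary analysis only if she was HSV-2 negative at baseline and has an 18-month result, so all three losses come out of the 104. What is at stake is whether the design delivers the 70 per cluster on which its power figure rests, and how much of the margin above 80% remains. A reader who has to interpret a null result needs those two figures to be right.

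**Working it through.** **1. Reproduce the plan's enrolment target.** 20% + 10% + 18% = 48%. 70 x 1.48 = 103.6, rounded up to 104. 104 x 15 = 1560 per arm, and 104 x 30 = 3120. All of the plan's figures are recovered. Other ways of using all three rates do not give 104:

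- 70 x 1.20 x 1.10 x 1.18 gives 110.
- 70/(0.80 x 0.90 x 0.82) gives 119.
- 70/(0.80 x 0.72) gives 122.

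One two-rate combination also lands on 104 (70 x 1.18/0.80 = 103.25, rounded up). It leaves out the attrition that the inflation is said to cover.

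**2. Reproduce the plan's power.** The article does not name its formula. I used the Hayes-Bennett formula for matched pairs and proportions, with a two-sided 0.05 test assumed:

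c = 2 + (z_α/2 + z_β)² x V/(p0 − p1)², where V = [p0(1 − p0) + p1(1 − p1)]/m + k²(p0² + p1²).

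Inputs: p0 = 0.20, p1 = 0.13, k = 0.25, c = 15 pairs.

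- Binomial part: 0.16 + 0.1131 = 0.2731, divided by m.
- Between-cluster part: 0.0625 x (0.04 + 0.0169) = 0.003556.
- At m = 70: V = 0.003901 + 0.003556 = 0.007458.
- Pairs needed for 80% power: 2 + 7.849 x 0.007458/0.0049 = 13.95.
- Power with 15 pairs: Φ(√(13 x 0.0049/0.007458) − 1.96) = Φ(0.963) = 83.2%.

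The claim of more than 80% at 70 per cluster is reproduced.

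**3. What 104 enrolled is expected to yield.**

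- Losses in sequence: 104 x 0.80 x 0.90 x 0.82 = 61.4 per cluster. Per arm this is 1560 x 0.5904 = 921, against 70 x 15 = 1050, a shortfall of 12%.
- Attrition and nonresponse summed to one 28% follow-up loss: 104 x 0.80 x 0.72 = 59.9 per cluster.

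**4. Power at those sizes, same formula, 15 pairs.**

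| Analysable per cluster | Pairs needed for 80% | Power | Power, paired t with 14 df |
|---|---|---|---|
| 70 | 13.95 | 83.2% | 83.1% |
| 61.4 | 14.82 | 80.5% | 80.4% |
| 59.9 | 15.0 | 80.0% | 79.9% |

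Sixty per cluster is the smallest whole number that gives 80% with 15 pairs under the matched-pair formula.

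**The case against.** **The power claim survives.** The plan promises only more than 80%, and about 61 per cluster still gives 80.5%. This stands. A reader might infer that the trial is underpowered against its own target; the figures do not show that. They show a drop of just under three percentage points and a reserve reduced to almost nothing.

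**Nonresponse may mean refusal before enrolment.** The term is not defined, and the sentence giving the purpose of the inflation names only attrition and background prevalence. Participant Recruitment says enrolment went on until the intended number was reached, which would absorb refusals. On that reading 104 x 0.80 x 0.90 = 74.9, which is above 70. It is the weaker reading, because the 18% is needed to make up the 48% and is dated to the 18 months of the study. If it is nevertheless what was meant, the 48% needs a different justification. The ambiguity is real and has to be settled in the text.

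**Two stronger readings are not supported.**

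- A reader might take the whole 48% off the 104 and conclude that power falls clearly below 80%. The plan adds 48% to 70; it never subtracts 48% from 104. Doing so would require that no baseline-positive woman is ever lost, yet those women stay in follow-up and some of the losses will fall among them.
- A reader might set 119 against the cluster criterion ("had at least 110 AGYW aged 15-23 years who were out of school") and conclude that the smallest clusters could never supply 70. The 110 is an eligibility floor. The sizes of the selected clusters are not given, and the loss rates are planning estimates, not limits.

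**Conclusion.** The statement is wrong as written, with a modest consequence. The step from 70 to 104 uses an invalid inflation. At the plan's own rates 104 enrolled is expected to give about 61 analysable women per cluster (about 60 if the two follow-up losses are summed), a shortfall of 12% to 14% on 70. Power falls from 83.2% to about 80.5% (80.0% at 60).

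The size of the shortfall rests on the three stated rates and on nonresponse being loss after enrolment. The power figures also rest on the matched-pair formula and on a two-sided test, neither of which the article states. A one-sided test would give 89.9% at 70 and 88.0% at 61.4, so the direction and rough size of the change stay the same. The design, the recruitment and the analysis do not need to change.

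**What to change.** In the Sample Size section:

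- Keep 104 per cluster as the number enrolled. Enrolment took place in December 2017 and two follow-up rounds are complete, so replacing the target with 119 would misdescribe the trial.
- State that, at 20% baseline prevalence, 10% attrition and 18% nonresponse, 104 is expected to yield about 61 analysable women per cluster (about 921 per arm), with power of about 80%.
- Remove the implication that 104 enrolled gives 70 analysable.
- Define nonresponse. If it is loss after enrolment, the figures above apply. If it is refusal before enrolment, the expected number is about 75 per cluster, and the 48% inflation needs its own explanation.
- State the sample-size formula and whether the test is two-sided.

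The cost is a few sentences and a slightly less favourable power figure. No further recruitment or change to the analysis is needed.

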### Statistical Methods

The primary analysis will be the difference in outcome measure (proportion of HSV–2-negative AGYW who are still free of HSV-2 after 18 months of follow-up) from each matched pair of clusters across the two arms. Secondary analysis will report cumulative incidence rates using survival analysis techniques. We hypothesize that the communities receiving cash transfer will have a significantly lower cumulative incidence of HSV-2 than that of the villages not receiving the cash transfer.

HIV prevalence will be assessed by comparing the prevalence in the intervention arm against the prevalence in the control arm. The primary analysis will be the proportion of AGYW who are HIV+ at 18 months across the two arms. Secondary analysis will be performed using logistic regression analysis, adjusting for clustering and baseline HIV measurements. Cash transfer recipients are expected to have a significantly lower HIV prevalence than those in the control arm. A comparison of sexual behavior outcomes between the two arms will be made by a repeated measure logistic regression. The logistic model adjusted for clustering will be used to account for the clustering design.

Qualitative data will be analyzed following the grounded theory approach [36]. Themes will be identified through coding. Open codes will be used to capture a priori and emerging concepts. Open codes will be developed by two researchers after independently reviewing a limited number of transcripts based on emerging concepts. Following initial code development, the two researchers will compare themes and codes and develop a final coding scheme. The research team will meet to discuss emerging themes. After completing the coding for half of the transcripts, axial coding (ie, comparing code categories to the objectives of the study and findings from literature) will be applied to group open codes into abstract conceptual categories. In all, 10% of the transcripts will be double coded in NVivo to ensure consistency between coders. The two coders will discuss and agree upon quotations from participants that best represent the themes. The coding scheme will be documented in a codebook.

Queries will be performed in NVivo to analyze themes across participants to understand (1) how the desired impact was achieved by the interventions implemented and (2) the perceptions and acceptability of the interventions.

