### Participant Recruitment

In villages/*mitaa* identified as potential recipients of the cash transfer, the Sauti project conducted a household survey to identify out-of-school AGYW. Only AGYW identified through this survey constituted the population eligible for CTP and the study. This way, only AGYW who were already out of school before the initiation of the project were enrolled in the study. Following this survey, community meetings of AGYW and their caregivers were held as part of the Sauti project to introduce the study. Eligible AGYW were invited to attend SBCC training sessions. Eligible participants were as follows: AGYW aged 15-23 years, graduated from 10 hours of Sauti’s SBCC sessions, and resident of the village of recruitment. Other inclusion criteria were as follows: registered into CTP (applicable to those in the CTP areas only) and currently out of school (not enrolled in primary, secondary, or tertiary education; they either have never been to school or have dropped out of school at least 1 month before study enrollment), as documented through a previous household survey of the CTP. In addition, AGYW who were willing and able to give voluntary, informed consent/assent to all study procedures, including HIV and HSV-2 testing and receiving test results, were considered eligible. Consent from parent /guardian was required for AGYW who are younger than 18 years, with the exception of emancipated minors (ie, minors who are married, have given birth, or demonstrating full independence, eg, living alone or heading the household). AGYW found to be HIV- and HSV-2 positive at baseline or follow-up visit were not excluded from the study because excluding them is likely to disclose their HIV or HSV-2 serostatus to the community and therefore expose them to stigma and other social harms. Their data will also contribute to the analysis of the study behavioral outcomes (reporting of compensated sex and intergenerational sexual partnerships).

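### The lead HIV analysis is written as 18-month prevalence by arm, with adjustment for clustering and baseline HIV left to a secondary analysis and an expectation of significance the trial is not sized to meet

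*Protocol article*

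**What the plan says.** HIV is a secondary outcome and is defined as prevalence (Protocol article, Outcomes: "Secondary outcome measures include HIV prevalence, reporting of intergenerational sex"). Statistical Methods sets out two tiers for it. The lead tier reads "The primary analysis will be the proportion of AGYW who are HIV+ at 18 months across the two arms". The second reads "Secondary analysis will be performed using logistic regression analysis, adjusting for clustering and baseline HIV measurements". Neither mentions the matched pairs. In the same section, the HSV-2 primary analysis is limited to women negative at baseline and takes the difference "from each matched pair of clusters across the two arms".

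A later sentence, "The logistic model adjusted for clustering will be used to account for the clustering design", directly follows the repeated-measures model for sexual behaviour.

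On enrolment, Participant Recruitment says "AGYW found to be HIV- and HSV-2 positive at baseline or follow-up visit were not excluded from the study". On what to expect, Statistical Methods says "Cash transfer recipients are expected to have a significantly lower HIV prevalence than those in the control arm", while Sample Size explains that HSV-2 was chosen as a proxy "as the study would not be powered to detect a difference in HIV incidence in a relatively low-incidence setting such as Tanzania".

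**The concern.** The ranking of the two HIV analyses is stated in the article, so it is not a detail left to an unseen plan. Three things follow from it.

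1. **Baseline infections.** Women positive at baseline are still positive at 18 months in both arms. They add noise, they pull the prevalence ratio towards 1, and any chance imbalance between 15 and 15 villages goes into the lead estimate uncorrected.
2. **Clustering.** Villages were randomised. If the lead comparison treats women as independent, its standard error is too small.
3. **Expectation against power.** Prevalence is a more diluted measure than incidence. A trial described as unable to detect a difference in HIV incidence cannot reasonably expect a significant difference in prevalence.

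HSV-2 stands in for HIV incidence and the theory of change ends in fewer new HIV infections, so readers will look at the HIV result. A null finding could be read as a failed prediction when the trial was never sized for it.

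**Working it through.** **Inputs from the protocol article**
- 15 pairs; 104 enrolled per cluster, 1560 per arm; attrition 10% and nonresponse 18% (Sample Size). Taken as multiplicative: 1560 × 0.90 × 0.82 = 1151 per arm, about 77 per cluster.
- HSV-2: 20% against 13% at 70 per cluster, coefficient of variation (CV) k = 0.25 (Sample Size).
- Tanzanian HIV prevalence 1% at age 15-19 and 3.4% at 20-24; midpoint 2.2% (Background).

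**Assumptions, since no figure is given**
- HIV incidence: (3.4 − 1)/5 = 0.48 per 100 person-years, range 0.24-1.5.
- HIV CV: 0.25 borrowed from HSV-2; 0.5 as a sensitivity value only.
- Two-sided 5% tests.

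**Step 1. The plan's own figure.** Pairs = 2 + (1.96 + 0.84)² × V / (p0 − p1)², with V = p0(1 − p0)/70 + p1(1 − p1)/70 + k²(p0² + p1²) = 0.00746 and (p0 − p1)² = 0.0049. This gives 13.9 pairs for 80% power; 15 pairs give 83%. The stated power above 80% for HSV-2 is reproduced. No power or precision is stated for HIV.

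**Step 2. Share of 18-month positives infected before the cash.** Share = b / (b + new), where b is baseline prevalence and new = (1 − b)(1 − (1 − incidence)^1.5).

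| Baseline | New by 18 months at 0.48 | Share predating | Share at 0.96 | Share at 1.5 |
|---|---|---|---|---|
| 1% | 0.71% | 58% | 41% | 31% |
| 2.2% | 0.70% | 76% | 61% | 50% |
| 3.4% | 0.69% | 83% | 71% | 61% |

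At 0.24 per 100 person-years the shares are 74%, 86% and 91%. At 1% baseline and 1.0 per 100 person-years the share is 40%.

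**Step 3. Dilution and power.** Apply the HSV-2 effect, 1 − 13/20 = 35%, to new HIV infections at 0.48 per 100 person-years. The prevalence ratio becomes (b + 0.65 × new)/(b + new) = 0.85, 0.92 and 0.94 for the three baselines. Power with 1151 per arm, ignoring clustering, is about 5-7% for prevalence. It is about 12% for new infections in baseline-negative women, because only about 0.0070 × 1151 ≈ 8 new infections are expected in the control arm. Neither measure is powered.

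**Step 4. Chance baseline imbalance.** The standard deviation of the between-arm difference in baseline prevalence, ignoring clustering, is √(2b(1 − b)/1151). At b = 2.2% this is 0.61 percentage points. The effect sought in Step 3 is 0.35 × 0.70 = 0.25 points, so the baseline noise exceeds it.

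**Step 5. Clustering, if it is ignored.** Design effect = 1 + (77 − 1)ρ, with ρ = k²p/(1 − p); type I error = 2[1 − Φ(1.96/√design effect)].

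| HIV prevalence | k = 0.25: design effect, type I | k = 0.5: design effect, type I |
|---|---|---|
| 1% | 1.05, 5.6% | 1.19, 7.3% |
| 2.2% | 1.11, 6.2% | 1.43, 10.1% |
| 3% | 1.15, 6.7% | 1.59, 12.0% |
| 3.4% | 1.17, 7.0% | 1.67, 12.9% |

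A simulation of 15 pairs of 77 per cluster under no effect (40,000 runs, prevalence 2.2-3%) gave 6.3-6.7% at k = 0.25 and 10-12% at k = 0.5 for an unadjusted two-proportion test. With half the between-village variance lying between pairs, the figures fell to 5.6-5.9% and 7.6-8.8%. A paired test on cluster proportions stayed at 4.7-5.0%.

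**The case against.** The best defence is that the lead sentence names an outcome and a time point, not a test. No standard error or interval method is written, and a condensed article may leave that to the full plan. That stands. A reader might infer that the HIV interval will be too narrow, but the documents do not establish it; the inflation in Step 5 is conditional. It is also modest at the only CV the documents contain. The 10-12% figure needs a CV of 0.5, which appears nowhere in them.

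A reader might also count ignored pairing as a cause of false precision. The direction is the reverse: where matching works, ignoring it makes a test more conservative and offsets part of the clustering error.

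Two further readings go too far. That the outcome must mostly count old infections fails at 1% baseline with incidence near 1 per 100 person-years. The 64% reduction that Background quotes from the Malawi cash transfer trial is an effect on prevalence, so it should not be applied to incidence and then shown as diluted.

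Finally, HIV is secondary, Sample Size is candid about power for incidence, and a model adjusted for clustering and baseline HIV is already planned. All true, and this limits the severity. What remains is that the weaker analysis is ranked first and that the expectation of significance contradicts Sample Size. The sentence on a clustering-adjusted logistic model does not settle the matter, since it follows the behavioural outcomes and the lead HIV comparison is not described as a logistic model.

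**Conclusion.** The point holds in limited form and should be fixed. As written, the lead HIV result has no stated term for cluster, pair or baseline, although villages were randomised and baseline-positive women are kept. It therefore retains chance baseline imbalance and is diluted by infections that predate the cash: 58-83% of 18-month positives at 0.48 per 100 person-years and 1-3.4% baseline, and 31-91% across the wider incidence range. These shares rest on an assumed incidence and on national prevalence figures. If clustering is ignored, type I error is about 6-7% at the borrowed CV of 0.25, less if matching is effective and more if HIV varies more between villages.

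The conflict between expecting a significant prevalence difference and being unpowered for incidence needs no assumption. The HSV-2 primary analysis is paired and restricted to baseline-negative women, so the trial's main conclusion is untouched.

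**What to change.** In Statistical Methods:

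1. Make the planned model adjusted for clustering and baseline HIV the lead HIV analysis, with the matched pairs respected. State how baseline HIV enters. Since infection does not revert, an individual-level term nearly determines the outcome in women positive at baseline, and the arm effect then rests on those who were negative.
2. Report the unadjusted 18-month proportions by arm as descriptive only, without a test.
3. Add new HIV infections among baseline-negative women, analysed by the same matched-pair method as HSV-2, as a supportive analysis. HIV is tested at baseline and at 6, 12 and 18 months, so no new data are needed.
4. Replace the expectation of a significant difference with a statement that the HIV effect is estimated with a 95% CI and is not powered.

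Cost: items 1, 2 and 4 change wording and ranking only. Item 3 is not wording alone. Two follow-up rounds are complete and analysts are unblinded, so it must be dated and labelled as added after follow-up began, and it should not replace prevalence as the declared secondary outcome. The HIV result becomes explicitly exploratory.
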